## Abstract

**Background:**

Sleep disorders are a risk factor for developing a variety of mental disorders, have a negative impact on their remission rates and increase the risk of relapse. Early identification and treatment of sleep disorders is therefore of paramount importance. Unfortunately, in mental health care sleep disorders are often poorly recognized and specific treatment frequently occurs late or not at all. This protocol-paper presents a randomized controlled trial investigating the clinical relevance of early detection and treatment of sleep disorders in mental health care. The two aims of this project are 1) to determine the prevalence of sleep disorders in different mental disorders, and 2) to investigate the contribution of early identification and adequate treatment of sleep disorders in individuals with mental disorders to their sleep, mental disorder symptoms, general functioning, and quality of life.

**Methods:**

Patients newly referred to a Dutch mental health institute for psychiatric treatment will be screened for sleep disorders with the self-assessment Holland Sleep Disorders Questionnaire (HSDQ). Patients scoring above the cut-off criteria will be invited for additional diagnostic evaluation and, treatment of the respective sleep disorder. Participants will be randomly assigned to two groups: Immediate sleep diagnostics and intervention (TAU+SI-T0), or delayed start of sleep intervention (TAU+SI-T1; 6 months after inclusion). The effect of sleep treatment as add-on to treatment as usual (TAU) will be tested with regard to sleep disorder symptoms, general functioning, and quality of life (in collaboration with a psychiatric sleep centre).

**Discussion:**

This trial will examine the prevalence of different sleep disorders in a broad range of mental disorders, providing information on the co-occurrence of specific sleep and mental disorders. Further, this study is the first to investigate the impact of early treatment of sleep disorders on the outcome of many mental disorders. Moreover, standard sleep interventions will be tailored to specific mental disorders, to increase their efficacy. The results of this trial may contribute considerably to the improvement of mental health care.

**Trial registration:**

This clinical trial has been retrospectively registered in the Netherlands Trial Register (NL8389; https://www.trialregister.nl/trial/8389) on February 2th, 2020.

## Background

Sleep problems are among the most frequent complaints in individuals with a mental disorder. Therefore, sleep disorders are common in individuals with mental disorders. Chronic insomnia, for example, is estimated to affect more than 40% in schizophrenia spectrum disorders [1], compared to approximately 6% in the general population [2]. Furthermore, insomnia complaints were reported in more than 50% in individuals with an affective disorder [3]. Six categories of clinical sleep disorders are identified in the International Classification of Sleep disorders (ICSD-3); insomnia, sleep related breathing disorders (SRBD), central disorders of hypersomnolence (hypersomnia), circadian rhythm sleep-wake disorders (CRSD), parasomnias, and sleep-related movement disorders [4]. Although insomnia prevalence has been investigated in connection with several different mental disorders, prevalence rates for the other categories of sleep disorders have been less or not at all studied in connection to the presence of mental disorders. More detailed information on the prevalence of a certain sleep disorder in connection to particular mental disorders could improve treatment strategies and may even lead to the identification of novel etiological pathways underlying the respective sleep disorders.

Studies suggest that sleep disorders increase the risk for the development of mental disorders, and worsen treatment outcome [5–7]. For instance, insomnia has been shown to have prognostic validity for the development of posttraumatic stress disorder (PTSD) [6, 8] and depression [9, 10]. Moreover, the already high vulnerability for suicidal behavior in individuals with mental health problems is further increased in those with poor sleep [11, 12]. Thus, early and adequate treatment of sleep disorders in individuals with mental disorders may be of paramount importance, and might well lead to better mental health outcomes and improved quality of life.

Despite the widespread use of sleep medication in psychiatry, cognitive behavioral therapy for insomnia (CBT-I) is currently considered the first-choice treatment of chronic insomnia. CBT-I consists of psychoeducation, sleep hygiene, relaxation training, stimulus control therapy, sleep restriction therapy and cognitive therapy. CBT-I is safe and effective (reviewed in [13]), with superior long-term effects compared to sleep medication (in [14]). In individuals with both insomnia and depression, CBT-I was found to both alleviate insomnia complaints and reduce depression severity [15–18]. Furthermore, in individuals suffering from posttraumatic nightmares, the treatment of nightmares with imagery rehearsal therapy (IRT) showed promising results in reducing both insomnia and nightmare frequency, as well as other global PTSD symptoms [19]. Although these standard sleep disorder treatments are successful in the general population, within individuals with mental disorders problems with compliance may arise, for example because the commonly used procedures may elicit distress that interferes with the efficacy of treatment. Therefore, treatment protocols used in this study were adapted to better fit the targeted population.

Despite a high occurrence of sleep disorders and established negative effects on mental health, little attention is paid to sleep problems in mental health care. Sleep disorders are frequently diagnosed years after onset; years in which poor sleep already exerted detrimental effects on physical and mental health, daytime functioning and quality of life. Clearly, a lot can be gained in mental health care by a timely delivery of sleep disorder treatment. This paper presents the protocol of a randomized controlled trial, in which the prevalence of distinct sleep disorders will be assessed and the clinical relevance of early sleep disorder treatment in mental health care will be tested.

### Aims and objectives

The overall aim of this study is to investigate the clinical relevance of early identification and adequate treatment of sleep disorders that co-occur with mental disorders.

The primary objectives of the study are to investigate:

1) The prevalence of the different six categories of sleep disorders (insomnia, SRBD, hypersomnia, CRSD, parasomnias, and sleep-related movement disorders) in connection to specific mental disorders.

2) Whether screening for and early treatment of sleep disorders exerts positive effects on sleep, treatment outcomes (symptom severity/remission of mental disorder), and quality of life.

Sex differences in both sleep and mental disorders are common; therefore, the effect of sleep disorder treatment may differ between the sexes. Based on this, a secondary objective of this study is to investigate whether there is an interaction effect between sex and treatment of sleep disorders on sleep, mental disorders symptoms (symptom severity/remission of mental disorder), and quality of life.

## Methods

### Design

This study is designed as a randomized controlled trial in order to test the effects of early interventions for sleep disorders on both sleep problems and mental health outcome. Participants will be asked to complete several questionnaires concerning sleep, quality of life, general functioning and specific mental disorder symptomatology, at three different time points over the course of twelve months. Researchers and study participants are not blinded to the conditions of the study.

### Study population

All treatment seeking individuals who are newly registered at GGZ Drenthe Mental Health Institute (GGZ Drenthe, Assen, NL; https://ggzdrenthe.nl/) will be asked to participate in this study by their treating therapist. The population of this mental health institute consists of individuals diagnosed with a variety of mental health disorders. Most individuals are diagnosed with chronic and/or complex mental disorders and often present with co-morbid disorders. Based on the participants’ main diagnosis according to the *Diagnostic and Statistical Manual of Mental disorders -* Fifth edition (DSM–5) [20], participants will be subdivided into the following diagnostic groups: depressive disorder, bipolar disorder, anxiety disorder, PTSD, attention deficit (hyperactivity) disorder (AD(H)D), autism spectrum disorder (ASD), schizophrenia spectrum disorder (SSD), or personality disorder. Patients under the age of 18, unable to adequately read or speak Dutch, and/or deemed unfit (by their therapist) to fill out questionnaires will be excluded from the study.

### Procedure

As part of the intake procedure of the mental health institute, routine outcome assessment (ROA) measurements are conducted in most departments of the institute, using an established online platform [21]. We will use this infrastructure, to reduce the burden to the participants and ensure data quality. Participants will be asked to complete questionnaires prior to the intake procedure (T0), 6 (T1), and 12 (T2) months later.

To screen for sleep disorders, patients fill out the Holland Sleep Disorders Questionnaire (HSDQ) [22, 23]. Patients who score above the cut-off score for any specific category of sleep disorders will be invited to participate in this study. After being informed about the study procedures, they will be asked for informed consent.

For both the experimental and control conditions, participants will continue their treatment as usual (TAU) throughout the study. After stratification for type of mental disorder, participants will be randomly assigned (using Sealed Envelope software) to either the experimental or control condition. In the experimental condition sleep intervention(s) (SI) will start immediately at T0 (TAU+SI-T0). In the control condition, the sleep intervention(s) will first start six months after inclusion, at T1 (TAU+SI-T1). This allows to test the effects of early interventions for sleep disorders on mental disorder symptoms, general functioning, sleep, and quality of life. Sleep interventions generally start with extensive diagnostic evaluation, followed by patient-targeted sleep treatment. For individuals scoring below the cut-off score for a sleep disorder on the HSDQ, participation is limited to filling out the questionnaires at T0. An exception to randomised allocation will be made for participants in the control condition whose HSDQ result or intake interview indicates a very severe sleep disorder, such as Narcolepsy. These participants will be immediately referred to a sleep centre, regardless of original randomization. These patients will be included in the prevalence estimate, but excluded from the analysis of the treatment effects. An overview is provided in Fig. 1.

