### Sample size calculations

Power analysis were performed using G*Power software [45]. Based on previous studies [18, 46], we aim at an effect size of 0.4 (Cohen’s d) for the outcome variables “quality of life”, “general functioning” and “mental disorder specific symptoms”. Power analysis based with an α of .05 and a power of .8, resulted in a required group size of 48 patients per diagnostic group (24 TAU+SI-T0 and 24 TAU+SI-T1). Due to limitations in recruitment capacity in less prevalent disorders, differences across both sexes will only be examined in the relatively high prevalent disorders: depression and PTSS. Power analysis with a 2 × 2 experimental group design (TAU+SI-T0 versus TAU+SI-T1; and males versus females) as between subject factors and the three time points as within subject factors suggests that with an α of .05 and a power of .8 a group size of 92 per group (46 TAU+SI-T0 and 46 TAU+SI-T1) would be sufficient. This analysis assumes an equal sex distribution. Overall, a total of 472 participants will be included in this study (overview provided in Table 2).

**Table 2 Tab2:** *Overview of targeted sample-sizes per diagnostic category*

Group	Prevalence (%)	Sec. analysis: yes/no	Required number per experimental group	Total required number per diagnostic subgroup	% of total population needed to include
**Depression**	17	Yes	46	92	15.0
**Bipolar disorder**	3	No	24	48	44.4
**Anxiety disorder**	10	No	24	48	13.3
**PTSD**	15	Yes	46	92	18.1
**ADHD/ADD**	9	No	24	48	14.7
**ASD**	4	No	24	48	33.1
**SSD**	5	No	24	48	26.7
**Personality disorder**	6	No	24	48	22.3
**Total**			**236**	**472**	

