#### Effect of sleep disorder treatment

Nearly all sleep disorders induce disturbed sleep and consequently result in a sleep deficit. We hypothesize that the sleep deficit, rather than the underlying disorder, may be most influential on the added burden of the sleep disorder on the patient’s mental well-being. Therefore, in the analysis of the effects of added sleep interventions, no distinction will be made between the different all types sleep disorders and all treatments will be lumped together. The effects of added sleep intervention in all participants with a sleep disorder will be assessed at six and twelve months by comparison of treatment (TAU-SI-T0 and TAU-SI-T1) groups over time (T0, T1, and T2). Secondary analysis will focus on the interaction between treatment effect and sex differences. For statistical evaluation linear mixed models, separate for all outcome parameters, will be employed. A stepwise approach will be followed in which first results for crude models will be taken, after which models including potential confounders such as age, sex, and social demographic parameters are run.

These analyses will be performed in the total population for the quality of life and general symptom outcome parameters, and in the eight mental disorder diagnostic subpopulations (depressive disorder, bipolar disorder, anxiety disorder, PTSD, AD(H)D, ASD, SSD and personality disorder) for the specific mental disorder symptom parameters. Due to power limitations, secondary analysis will only be performed within the more prevalent disorders: depression and PTSD.

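### Very severe cases are dropped after randomisation from the control arm only, so the arms compared for the treatment effect differ in severity by design

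*Protocol article*

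**What the plan says.** Under Procedure, participants are stratified by type of mental disorder and then randomised to TAU+SI-T0 or TAU+SI-T1. An exception follows, which begins: "An exception to randomised allocation will be made for participants in the control condition whose HSDQ result or intake interview indicates". What has to be indicated is a sleep disorder judged very severe, and narcolepsy is the one example given. On these participants the article says: "These participants will be immediately referred to a sleep centre, regardless of original randomization". It then fixes how they are handled in the analysis: "These patients will be included in the prevalence estimate, but excluded from the analysis of the treatment effects".

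For the other arm the section says only: "In the experimental condition sleep intervention(s) (SI) will start immediately at T0 (TAU+SI-T0"). It makes no exception by severity there. Under Effect of sleep disorder treatment the comparison is described broadly: "The effects of added sleep intervention in all participants with a sleep disorder will be assessed at six and twelve months", by arm over T0, T1 and T2, using linear mixed models. These are run crude first and then with potential confounders such as age, sex and sociodemographic variables. Severity of the sleep disorder is not among the examples.

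The Design section states: "Researchers and study participants are not blinded to the conditions of the study".

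**The concern.** The rule is an exclusion after randomisation, defined by a prognostic feature and worded for one arm. Randomisation makes the arms alike in expectation on sleep-disorder severity, and this rule undoes that. The control arm loses its most severe members, while nothing in the article removes their counterparts from the immediate arm.

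Two features make it harder to dismiss. First, very severe is not defined. Narcolepsy is given as an example, but the trigger is any HSDQ result or intake interview judged to fit, so the number removed has no stated bound. Second, the rule can be applied only by someone who knows that the participant is a control, and the trial is unblinded. The judgement can therefore depend on the allocation.

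At stake is the second primary outcome, the effect of sleep interventions on sleep, symptoms, functioning and quality of life, in every between-arm comparison.

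**Working it through.** **Step 1. The rule for each arm, side by side.**

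| | TAU+SI-T1 (control) | TAU+SI-T0 (immediate) |
|---|---|---|
| Very severe at HSDQ or intake | Referred at once | Starts sleep intervention at T0 like the rest of the arm |
| Prevalence estimate | Included | Included |
| Treatment-effect analysis | Excluded | No exclusion stated |

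The lower right cell is an inference from the wording of the exception and the absence of a mirror rule. The section on missing data adds two further exclusions from the treatment part: controls who fall below the HSDQ cut-off at T1, and participants whose disorder the diagnostic work-up does not confirm. Neither removes very severe cases from the immediate arm.

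**Step 2. Size, for scale only.** The plan states no figure on this point, so there is none to reproduce.

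Inputs from the protocol:
- 236 per arm and 472 in total (Table 2)
- planned Cohen's d of 0.4 ("we aim at an effect size of 0.4")
- α of .05, taken here as two-sided, which the protocol does not state

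Inputs assumed, because the protocol gives none:
- share p of very severe participants, 1% to 10%
- outcome gap D between them and the others, 0.5 to 1.5 SD

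With no treatment effect, the immediate arm has mean p × D relative to the other participants, and the control arm has mean 0 once its severe cases are removed. Hence:

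- shift b = p × D
- se = √(1/236 + 1/(236(1 − p)))
- type I error = Φ(−1.96 − b/se) + 1 − Φ(1.96 − b/se)

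Example with p = 5% and D = 1: b = 0.05; se = √(1/236 + 1/224.2) = 0.093; b/se = 0.54; type I error = .084.

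| p | Controls removed of 236 | D = 0.5: shift; type I error | D = 1.0 | D = 1.5 |
|---|---|---|---|---|
| 1% | 2.4 | 0.005; .050 | 0.010; .051 | 0.015; .053 |
| 2% | 4.7 | 0.010; .051 | 0.020; .055 | 0.030; .062 |
| 5% | 11.8 | 0.025; .058 | 0.050; .084 | 0.075; .127 |
| 10% | 23.6 | 0.050; .083 | 0.100; .185 | 0.150; .354 |

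As a share of the planned 0.4, the shift runs from 0.005/0.4 = 1.2% to 0.15/0.4 = 37.5%. In a diagnostic group with 24 per arm, 1% to 10% is 0.24 to 2.4 controls.

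**Step 3. What the table does not show.** It treats the outcome as a single raw comparison. The planned models compare the arms over time, so a pure difference in level at T0 largely drops out of the group-by-time contrast. If D is read as the gap in *change* from T0 between severe and other participants, the same formula applies. If that gap is zero, the shift in the contrast is zero.

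**Step 4. After the fix.** With everyone analysed as randomised, or one T0 criterion applied to both arms, this rule no longer makes the arms differ and b = 0. The first option costs some dilution. If early-referred controls gain the full effect by T1, the expected contrast is 0.4 × (1 − p), which is 0.396 at 1% and 0.36 at 10%.

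**The case against.** The strongest defence is that the rule probably touches very few people. The only example is narcolepsy. At 1% with a gap of 1 SD, about two of 236 controls are removed, the shift is 0.01 SD and the type I error is .051. The mixed model reduces the effect further where severity changes the level and not the course. All of this stands as a statement about size. It does not justify a one-sided rule, because the category has no threshold that would keep it small.

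A reader might also infer more than the documents support:

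- *That the protocol says severe immediate-arm participants are analysed.* It does not say so outright. The inference is the natural one, but it rests on the absence of a mirror rule in a condensed article.
- *That the bias has a known direction.* Severe cases may do worse, or may have more room to improve. The separate removal of controls who drop below the HSDQ cut-off at T1, if it carries into the analysis, takes improvers out of the same arm, so the net imbalance in severity is not established.
- *That the damage cannot be repaired in analysis.* The HSDQ is completed at T0 in both arms, so counterparts flagged on the HSDQ can be found. Only cases flagged solely at the intake interview may be harder to match.
- *That the check can simply be moved ahead of randomisation with the referral rule unchanged.* The HSDQ precedes the invitation, but the article does not say whether the intake interview precedes allocation. Such a move would also change who is referred and who is randomised, which is a clinical and population question on which no view is taken here.

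**Conclusion.** The point holds. Followed as written, the plan compares an immediate arm that by inference keeps its very severe cases with a control arm from which they have been removed after randomisation, on an undefined criterion, in an unblinded trial. This is a rule stated wrongly and not a detail left to an analysis plan.

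The direction is unknown and the size cannot be read from the documents. Under the assumed ranges the raw shift is 0.005 to 0.15 SD, with type I error from .050 to .354 at 236 per arm. The low end is the more plausible if only narcolepsy-like cases qualify. The group-by-time contrast is affected only to the extent that change over time differs by severity. The fault lies in the exclusion from analysis; the early referral itself is not in question.

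**What to change.** Under Procedure, replace the exclusion of these controls from the treatment-effect analysis with a statement that all randomised participants are analysed in the arm assigned, including controls referred early. Leave the referral as it is. Their T1 and T2 questionnaires are needed for this, and nothing in the article says that these stop on referral.

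Add a sensitivity analysis that excludes very severe cases from both arms by one pre-specified criterion, based on T0 data held for both arms, such as the HSDQ. Define that criterion for analysis before outcome data are examined.

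The cost is a change of one sentence and one additional analysis. The downside is the slight dilution shown in Step 4, because controls referred early receive sleep care before T1. The other exclusions in the missing-data section are not settled by this change and should be checked for consistency with it.

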**Fig. 1 Fig1:**
[figure not shown]
Study procedure. Patients who score above the cut-off score for any type of sleep disorder on the Holland Sleep disorders Questionnaire (HSDQ+) will be invited for extensive diagnostic evaluation, followed by patient-targeted sleep treatment. Those participants will be randomly divided in one of two conditions: in TAU+SI-T0 sleep diagnosis and sleep intervention (SI) will start immediately (T0), in addition to the treatment as usual (TAU). In TAU+SI-T1 sleep diagnosis and SI will start after 6 months (T1). Questionnaires will be filled in at T0, T1 and T2 (after 12 months), measuring sleep, general functioning, specific mental disorder symptoms, and quality of life. For patients scoring below the cut-off score for a sleep disorder (HSDQ-), participation is limited to filling out the questionnaires at T0

This research project will be conducted in collaboration with a sleep centre for psychiatry. Anamnestic interviews, diagnostic assessments and sleep interventions will be provided by trained staff.

